### Intervention Description

As aforementioned, the VR-SIM Carers MVP is a self-paced, VR-based training tool designed to support family caregivers and care partners of people living with dementia in developing practical caregiving strategies through immersive simulation–based learning. The MVP consists of three key components:

Functional system menu: Upon entering the VR-SIM Carers platform, users are greeted with a brief narration describing how to select and start a scenario. Users may select from 1 of 3 scenarios.Three high-fidelity VR scenarios: They allow for simulation-based learning and practice. Users choose from responses presented to them to move forward in the scenarios, while receiving real-time guidance and feedback from 2 nonplayer characters in the VR scenario: a virtual clinician (Figure S1 in Multimedia Appendix 1) and a simulated person living with dementia (a virtual character playing the role of a person living with dementia in different settings). The 3 scenarios included are as follows:Managing Apathy (Figure S2 in Multimedia Appendix 1): The user will learn strategies to interact with a “mother” character displaying symptoms of apathy.Crisis Response (Figure S3 in Multimedia Appendix 1): The user will respond to and problem-solve a possible fire-hazard situation and interact with a “father” character who may be unaware of the smoking pan in the kitchen.Refusal of Care (Figure S4 in Multimedia Appendix 1): The user will interact with a “father” character who is displaying resistance to care, specifically refusal to get dressed.Feedback and reflection: To reinforce users’ learning after scenario completion, custom feedback is provided by a holographic clinician avatar and simulated person living with dementia within the same scenario environment, based on the particular decisions selected by the user. Immediate feedback and guided reflections from these characters will help caregivers understand the emotional and practical implications of their decisions.

The intervention is intentionally designed to be self-paced and may be repeated to reflect real-world use by caregivers. No minimum exposure dose is specified beyond prespecified adherence thresholds, which are used solely to inform feasibility. Exposure will be operationalized descriptively using engagement metrics including the number of scenarios completed, total time spent in scenarios, and whether virtual clinician feedback was reviewed. These metrics will be summarized to characterize the patterns of use and feasibility. No post hoc exposure-based subgroup analyses or inferential dose-response analyses are planned, since such analyses would risk bias and overinterpretation in a small pilot sample.

### Participants

Participants will be recruited from various partner sites and complete an expression of interest form to self-refer to the study. Partner sites are responsible for sharing our research ethics board (REB)-approved recruitment material for this study. To be eligible to participate, the following inclusion criteria should be met:

18 years of age or older.Able to provide informed consent.Current unpaid family caregivers or care partners of people living with dementia.Caring for an individual with either suspected or diagnosed dementia. A formal diagnosis is not required.No self-report of active or unstable major psychiatric conditions (eg, major depressive disorders, bipolar disorder, schizophrenia). The study co-principal investigator or joint senior author and geriatric psychiatrist AMB will make the final decisions if necessary.Able to read and speak English and able to (1) participate in prototype testing, (2) participate in a postintervention feedback survey, and (3) follow instructions from research staff and complete self-administered surveys or assessment tools.

### Study Enrollment and Timeline

Upon enrollment in the study, participants will complete three key activities (Textbox 1):

In-person orientation session: The study team led by primary author (MC) will guide participants one-on-one on how to safely use and take care of a VR-SIM Carers VR headset. A commercially available VR headset (Meta Quest 3), with the VR-SIM Carers software installed, will be loaned to participants for 4 weeks; a user manual and other supplementary materials will also be provided for review.Complete high-fidelity simulation scenarios: Using the VR headset, participants will engage in a series of self-paced immersive scenarios—Managing Apathy, Crisis Response, and Refusal of Care—that represent caregiving situations commonly encountered by family caregivers or care partners of people living with dementia. Participants will review the user manual to guide the completion of the 3 caregiving scenarios (8-10 minutes each) on the VR-SIM Carers headset at their own pace. After completing the scenarios, users will write reflections in the user manual following predefined prompts.Self-assessment tools: Participants will complete a set of 9 brief, self-assessment tools (20-30 minutes) at 3 time points (before, after, and 1 month after completing the VR scenarios). These will be emailed to participants and delivered through SimpleSurvey [23].

Textbox 1.Timeline or workflow of research activities to be completed by study participants.
**Week 1: In-person orientation event (90 min)**
In-person visit at the recruitment siteComplete REB-approved consent form and baseline assessment scales (via SimpleSurvey)Sign out study VR headset; complete orientation RE: headset use led by the study team. Complete Simulator Sickness Questionnaire
**Weeks 2 and 3: Self-paced learning on VR-SIM Carers**
Self-completion of VR simulation scenariosReview virtual clinician’s feedback; program resourcesComplete check-in phone call from the study team
**Week 4: In-person visit by study team (1 h)**
Complete time 2 assessment scales (via SimpleSurvey)Semistructured interview to capture participants’ experience with VR-SIM CarersReturn study virtual reality headset; submit written reflection notes
**One month after**
Complete time 3 assessment scales (via SimpleSurvey)Provide written feedback on overall study experience (via SimpleSurvey)

### Sample Size

Thirty caregivers will be recruited for the study. A cohort of 5 caregiver participants will be recruited from each recruitment site for equal representation, and enrollment will continue until the targeted number is reached. Recruitment sites are Ontario Shores Centre for Mental Health Sciences in Oshawa, Ontario; Baycrest Centre in Toronto, Ontario; Carefirst Community & Senior Services Association, in Toronto, Ontario; London Health Sciences Centre in London, Ontario; and St. Mary’s Hospital in Montreal, Quebec. Recruitment will take place once local ethics clearance has been received from each site’s research ethics board.

### Power Calculation

Based on previous literature, a minimum sample size of 20 participants has been identified as appropriate for a pilot study to provide preliminary estimates of variability and to evaluate key feasibility parameters. These estimates are informed by existing caregiver pilot study interventions [24,25]. To account for expected attrition, a total sample size of 30 participants will be recruited. This target provides a buffer to maintain the minimum sample needed to evaluate feasibility outcomes and to estimate variance for future sample size calculations, while accounting for potential data loss due to loss to follow-up.

### Progression Criteria

We prespecified quantitative and qualitative progression criteria to guide decisions about whether to proceed to a future definitive trial. Key thresholds are recruitment success 80% or higher (≥24/30 participants) of the target, amend-and-reassess if 50% to 79% (15-23/30) are enrolled, and stop or redesign if less than 50% (<15 participants) are enrolled. Retention success is 80% or higher completion of both postintervention and 1-month follow-up assessments, amend if 60% to 79% (18-23/30) complete, and stop if less than 60% (<18 participants). Intervention adherence success is 75% or more of the participants (≥23/30 participants) completing at least 2 of 3 scenarios and reviewing virtual clinician feedback during the loan period, amend if 50% to 74% (15-22/30), and stop if less than 50% (<15 participants). Data completeness success is 90% or higher (≥27/30) at baseline and 80% or higher (≥24/30) at post-intervention and 1-month follow-up for primary caregiver measures; amend for baseline 75% to 89% (≥23/30) or post-intervention or 1-month 60% to 79% (18-23/30). Safety or tolerability success is 15% or lower (<4 participants) reporting moderate or severe simulator sickness or adverse events attributable to device or software and no serious adverse events, amend if 16% to ‐30% (5-9/30) report moderate symptoms that are remediable, or stop if more than 30% (>9 out of 30 participants) report moderate or severe symptoms or any serious adverse event attributable to the intervention. Acceptability success is 70% or higher (≥21/30 participants) reporting willingness to use the MVP again or recommend it, amend if 50% to 69% (15-21/30), or stop if less than 50% (<15/30). Qualitative signals from interviews, reflection notes, and field notes will be used alongside these thresholds to interpret feasibility. Decision rules are to proceed to a definitive trial without substantive changes if most key criteria meet success thresholds, proceed with specified protocol modifications if criteria fall in the amend range but no major safety signals exist, and stop and redesign if multiple key criteria fall in the stop range or qualitative data reveal fundamental, unresolvable concerns. All progression decisions will be reported and justified in the Results section, and the CONSORT pilot flow diagram will present numbers screened, enrolled, completed at each time point, and the reasons for nonparticipation or dropout.

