## Results

The forthcoming results of this pilot study will provide preliminary evidence on the feasibility, acceptability, tolerability, and preliminary efficacy of the VR-SIM Carers MVP as a psychoeducational tool for family caregivers of people living with dementia. Quantitative results will report on changes in caregiver competence, resilience, empathy, and stress across 3 time points (baseline, postintervention, and 1-month follow-up), as well as secondary outcomes, such as caregiver burden, quality of life, depressive symptoms, and perceptions of behavioral disturbances in people living with dementia. These findings will indicate whether the VR-SIM Carers intervention holds promise in improving psychosocial outcomes for caregivers, while also highlighting areas for refinement prior to larger-scale trials.

Qualitative results, derived from interviews, reflection notes, and written survey responses, will complement the quantitative findings by exploring participants’ lived experiences with the intervention, including perceived benefits, usability, and barriers to engagement. Additional feasibility outcomes, including recruitment and retention rates, adverse events, and system usability scores, will further inform whether the MVP is suitable for broader testing.

Funding for the overall project commenced in September 2022, with funds for the study as described in this protocol paper coming in April 2024. Data collection began in March 2025 with a projected end date of March 2026. As of the submission of the manuscript (December 2025), 21 participants have been enrolled. Analysis of both quantitative and qualitative data is expected to be completed by April 2026. The results will then be published in fall 2026 through academic publications, conference presentations, and community-facing outputs, such as reports and project website updates. These findings will directly inform the next stage of intervention development and scaling.

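### Outside recruitment, the progression counts are right only for 30 participants, and nothing says whether count or percentage governs when fewer enrol

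*Protocol article*

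**What the plan says.** The Sample Size section sets the target: "Thirty caregivers will be recruited for the study", and "enrollment will continue until the targeted number is reached". The Progression Criteria section then pairs percentages with counts.

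- Recruitment: "recruitment success 80% or higher (≥24/30 participants) of the target"; 15 to 23 enrolled is amend, fewer than 15 is stop.
- Retention: success is 80% or more, with no count printed; then "amend if 60% to 79% (18-23/30) complete, and stop if less than 60% (<18 participants".
- Adherence: "Intervention adherence success is 75% or more of the participants (≥23/30 participants"; amend is 50% to 74% (15 to 22), stop is fewer than 15.
- Data completeness: "Data completeness success is 90% or higher (≥27/30) at baseline" and 80% (24) at the later visits; amend starts at 75% (23) at baseline and 60% (18) later. No stop band is printed.
- Safety: success is 15% or lower (fewer than 4), amend is 16% to 30% (5 to 9), stop is above 30% (more than 9).
- Acceptability: success is 70% (21), amend is 50% to 69% (15 to 21), stop is fewer than 15.

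Only recruitment has an explicit base, the target. For the other criteria the section does not say whether the base is the target, those enrolled or those assessed. It also does not say which form decides when the two differ. The Results section reports that "21 participants have been enrolled" as of December 2025, with data collection projected to end in March 2026.

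**The concern.** The plan defines bands for finishing below 30, so it foresees a smaller denominator, but its other counts do not move with it. The same result can then be classed one way by percentage and another by count. Feasibility is the stated primary focus and these thresholds are its decision rule. If the choice between the two forms is left open, it can be made after the data are seen, which defeats the purpose of prespecifying them. If the counts are applied as printed, a recruitment shortfall already judged under its own criterion is charged again under retention, adherence, completeness and acceptability.

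**Working it through.** **Inputs.** All thresholds come from the Progression Criteria section. N = 24 is the smallest enrolment counted as recruitment success. N = 21 is the December 2025 figure in the Results section.

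**Convention.** The bands are printed in whole percentages, so a value such as 79.2% lies between amend and success. I class anything at or above the amend floor and below the success threshold as amend.

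**Step 1: reproduce the printed counts at N = 30.** Smallest count meeting a percentage = percentage × 30, rounded up.
- Retention: 0.60 × 30 = 18. The amend band ends at 23, so success is implied from 0.80 × 30 = 24.
- Adherence: 0.75 × 30 = 22.5, so 23; 0.50 × 30 = 15.
- Baseline completeness: 0.90 × 30 = 27; 0.75 × 30 = 22.5, so 23. Later visits: 24 and 18.
- Acceptability: 0.70 × 30 = 21; 0.50 × 30 = 15.
- Safety stop: 0.30 × 30 = 9, so above 9.

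All of these agree with the text. Two other entries do not fit even at 30. Four safety reports (4/30 = 13.3%) meet the 15% limit but not the fewer-than-4 count, and sit in no count band. Acceptability of 21 lies in both the success and the amend counts.

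**Step 2: the same percentages at 24 and 21.** Success threshold / amend floor:

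| Criterion | Printed counts | N = 24 | N = 21 |
|---|---|---|---|
| Retention | 24 (implied) / 18 | 20 / 15 | 17 / 13 |
| Adherence | 23 / 15 | 18 / 12 | 16 / 11 |
| Baseline completeness | 27 / 23 | 22 / 18 | 19 / 16 |
| Later completeness | 24 / 18 | 20 / 15 | 17 / 13 |
| Acceptability | 21 / 15 | 17 / 12 | 15 / 11 |
| Safety, first count in stop | 10 | 8 (7.2 rounded up) | 7 (6.3 rounded up) |

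**Step 3: where the two forms disagree.**
- Retention, N = 24: 15–17 (62.5% to 70.8%) is amend by percentage, stop by count; 20–23 (83.3% to 95.8%) is success by percentage, amend by count. That is 3 + 4 = 7 of the 25 possible counts (0 to 24).
- Retention, N = 21: 13–16 is amend against stop; 17 (81.0%) is success against stop; 18–21 (85.7% to 100%) is success against amend. That is 4 + 1 + 4 = 9 of 22.
- Adherence: 8 of 25 disagree at 24 (12–14 and 18–22) and 10 of 22 at 21 (11–14 and 16–21). At 21, full adherence still misses 23.
- Baseline completeness: 24/24 misses 27; 21/21 is below even the amend floor of 23.
- Acceptability, counting 21 as success: 7 of 25 disagree at 24 and 10 of 22 at 21.
- Safety: 8–9 of 24 (33.3% to 37.5%) and 7–9 of 21 (33.3% to 42.9%) are stop by percentage, amend by count.

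**Step 4: effect on the overall decision.** Suppose 24 enrol, all give baseline data, none reports a safety event, and 20 are retained, adherent, complete at later visits and willing to use the program again. By percentage each of those four is 20/24 = 83% and baseline is 100%, so all seven criteria succeed (counting the two completeness limits separately). By count, retention, adherence, both completeness limits and acceptability are amend, leaving two of seven in success. The section's rule for proceeding without substantive changes needs most key criteria to succeed, so the outcome changes.

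**The case against.** The plan is for 30, enrolment is meant to continue until then, and 21 is an interim figure. If 30 enrol, the conflict described here disappears. That stands as intention, but the section itself defines outcomes for 15 to 29 enrolled. The other figures also make a shortfall plausible. The Sample Size section plans "A cohort of 5 caregiver participants will be recruited from each recruitment site for equal representation" and names five sites: 5 × 5 = 25. As an assumption, 21 enrolled over the 9 to 10 months since March 2025 is about 2.1 to 2.3 a month. Each participant needs about 4 weeks plus 1 month, so perhaps one to two months of enrolment remained, giving 21 + 2.1 = 23 to 21 + 4.6 = 26. The Abstract's start date of March 2024 would imply a slower pace. None of this proves a shortfall.

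A second defence is that 30 is always the denominator, or that the percentage leads and the bracket only illustrates it. Either would remove the conflict, but neither is stated. Adherence is expressed as a share of participants, and some limits are bare counts. Under a fixed base of 30, a study with 24 enrolled could pass retention only with no attrition (24/30 = 80%), although the Power Calculation section expects attrition.

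Third, the thresholds guide rather than dictate: qualitative findings are weighed alongside them and decisions must be reported and justified. This softens the consequence of one criterion shifting band. It does not settle which band applies.

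A reader might infer that every threshold fails at any enrolment below 30 and that the verdicts are opposite. The document does not support that.
- Recruitment is correctly out of 30, and retention success has no printed count.
- At 29, retention, later completeness and acceptability show no conflict. At 24, retention counts of 0–14, 18–19 and 24 agree.
- Most conflicts are between neighbouring bands. For retention, success against stop first appears at 21 enrolled.
- A fully adherent cohort of 21 or 24 is never stop on adherence.
- The safety count does not loosen throughout: fewer than 4 is what 15% allows at 21 (3.15) and 24 (3.6). Only the stop boundary becomes more lenient.

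**Conclusion.** The point holds for retention, adherence, data completeness, acceptability and the safety stop boundary. Their printed counts are correct only at 30, and with 24 or 21 enrolled, both inside the plan's own recruitment bands, percentage and count disagree for many results. For retention this affects 7 of 25 possible results at 24 and 9 of 22 at 21. The shift is usually one band, but it can change the overall progression decision. This is a conflict between two printed rules for the primary aim, not a detail left to another document, and it should be resolved before the criteria are applied. The conclusion assumes that the percentages refer to participants enrolled and that fewer than 30 enrol; if exactly 30 enrol, only the two separate slips found at 30 remain.

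**What to change.** Amend the Progression Criteria section as follows.

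1. Keep 30 as the denominator for recruitment only.
2. State that the percentages govern for retention, adherence, data completeness and acceptability, with all enrolled participants as the denominator, including dropouts and non-responders.
3. Delete the counts out of 30 for these criteria, or label them as illustrations for N = 30. If counts are wanted, derive them from the enrolment reached, as in the table above.
4. Reconcile the percentage and count forms of the safety criterion on one stated denominator, including the unassigned count of 4. No view is taken here on which safety limit is right.
5. Remove the overlap at 21 for acceptability in the same edit.

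The cost is one paragraph of wording and no new data. The downside is that the count thresholds are known only once enrolment closes.

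### Follow-up data completeness is confounded with retention (same assessments, same cut-offs, same denominator of 30), and completeness is the only progression criterion without a stop band

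*Protocol article*

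**What the plan says.** All the relevant thresholds are in the Progression Criteria section of the protocol article.

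- **Retention.** "Retention success is 80% or higher completion of both postintervention and 1-month follow-up assessments, amend if 60% to 79% (18-23/30) complete"; then "stop if less than 60% (<18 participants". The count for success is not printed.
- **Data completeness, baseline limb.** "Data completeness success is 90% or higher (≥27/30) at baseline".
- **Data completeness, follow-up limb.** "80% or higher (≥24/30) at post-intervention and 1-month follow-up for primary caregiver measures", with an amend band of 60% to 79% (18-23/30) at either follow-up assessment.
- **Data completeness, baseline amend band.** The text reads "amend for baseline 75% to 89% (≥23/30" and gives no upper count. No stop band is printed for either limb.
- **Decision rule.** The study proceeds without substantive change "if most key criteria meet success thresholds". It stops if several criteria are in the stop range. Six criteria are listed: recruitment, retention, adherence, data completeness, safety or tolerability, and acceptability. No weights are given, and no number is attached to *most*.

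Three other places bear on the point. The Methodological Approaches and Timeline section undertakes to report attrition, missing surveys and incomplete scales at each time point. The Outcome Measures section lists data completeness separately from retention. In Textbox 1, the one-month contact consists only of online survey forms.

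**The concern.** Retention and data completeness are listed as separate criteria and should answer separate questions: did participants stay, and did those who stayed give usable scale data? Because the follow-up limb of completeness is counted out of 30, a participant who has dropped out counts against both. At one month the overlap is close, since being retained means returning the same online survey whose completeness is then scored.

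Two things are at stake. First, dropout carries more weight than any other problem in a rule that appears to weigh six criteria equally. Second, the bands give the same answer whether the trouble lies in follow-up procedures or in the questionnaires, and these call for different changes before a definitive trial.

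Separately, the completeness bands do not cover all possible results. A poor enough result falls in no category, so the stop rule cannot use it.

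**Working it through.** **Inputs.** The denominator is 30 (Power Calculation: "To account for expected attrition, a total sample size of 30 participants will be recruited"). The bands are those listed above. The documents give no dropout rate and no rate of incomplete forms. Both are assumed below: dropout of 10% or 20%, and 0 to 10% of returned forms incomplete at each assessment.

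**Step 1: reproduce the counts.** 0.80 × 30 = 24; 0.60 × 30 = 18; 0.90 × 30 = 27; 0.75 × 30 = 22.5, rounded up to 23. The printed counts are reproduced. Retention success, which has no printed count, also means 24 of 30. Retention and the follow-up limb of completeness therefore share both cut-offs.

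**Step 2: logic when every returned form is complete.** Let *a* be the number completing both follow-up assessments, *b* post-intervention only, and *c* one month only. Retention succeeds if a ≥ 24. Follow-up completeness, read per assessment, succeeds if a + b ≥ 24 and a + c ≥ 24. All splits of 30 participants were enumerated.

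- Retention succeeds but follow-up completeness fails: 0 cases.
- Follow-up completeness succeeds but retention fails: 56 cases, with *a* as low as 18 (for example a = 18, b = 6, c = 6).
- If dropout is monotone (nobody who misses the first assessment returns for the second), the two always agree.

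Fewer than 24 participants at either follow-up assessment fails both criteria with certainty.

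**Step 3: allow incomplete forms.** This simulation used 400,000 replicates and monotone dropout, half of it before the post-intervention assessment. The same rate of incomplete forms applied at each assessment, baseline included. A returned form counted towards retention even if incomplete.

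| Dropout | Incomplete per assessment | Retention met | Follow-up completeness met | Completeness met, both limbs | Retention and follow-up completeness agree |
|---|---|---|---|---|---|
| 10% | 0 | 0.974 | 0.974 | 0.974 | 100% |
| 10% | 5% | 0.975 | 0.855 | 0.802 | 88% |
| 10% | 10% | 0.974 | 0.597 | 0.386 | 62% |
| 20% | 0 | 0.607 | 0.607 | 0.607 | 100% |
| 20% | 5% | 0.607 | 0.381 | 0.358 | 77% |
| 20% | 10% | 0.607 | 0.187 | 0.121 | 58% |

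The exact binomial probability of at least 24 of 30 is 0.974 at 90% retention and 0.607 at 80%, which matches the retention column. The disagreement runs one way: retention passes and completeness fails. Under monotone dropout, completeness cannot pass when retention fails.

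**Step 4: what the bands cannot distinguish.**

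- Case A: 23 complete both assessments, and 18 of them have complete scales at each. Among returners this is 18/23 = 78%.
- Case B: 18 complete both assessments, all with complete scales. Among returners this is 18/18 = 100%.

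Both cases score amend for retention (18-23/30) and amend for follow-up completeness (18/30).

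The Power Calculation section treats 20 participants as an adequate minimum. Ending with exactly 20 (20/30 = 67%), all with complete forms, puts both criteria in amend on dropout alone.

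**Step 5: the tally.** If dropout is the only problem, four of six criteria succeed. If one further criterion is in amend, three of six succeed. If completeness were scored among returners and passed, the latter would be four of six.

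**Step 6: gaps in the bands.** Baseline completeness of 22/30 or fewer, or follow-up completeness of 17/30 or fewer, has no category. The other five criteria each have a stop band. The Results section reports 21 enrolled by December 2025. If enrolment had ended there and the printed counts out of 30 governed, baseline completeness could not exceed 21/30 = 70%, which lies in no band.

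**The case against.** A reader might infer that the two criteria are one and the same count, and that completeness is not measured at all. The documents do not support that. Retention is joint over both assessments, while completeness reads most naturally per assessment and covers only the primary caregiver measures. Completeness also has a baseline limb that later dropout cannot affect. The table shows that incomplete forms can fail it on their own: at 10% dropout and 10% incomplete forms, retention is met with probability 0.974 and follow-up completeness with 0.597. Nor would scale-completion problems be hidden, because incomplete scale data are to be reported at each time point.

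A reader might also infer that counting dropout twice reverses the overall decision. That is not shown. With dropout alone, four of six criteria still succeed. The three-of-six case is a boundary example and depends on reading *most* as more than half. Qualitative findings are weighed alongside the thresholds, and decisions must be justified. Dropout also cannot count twice towards stopping, because completeness has no stop band.

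The baseline amend overlap is a slip in the count only, since the printed 75% to 89% shows the intended limit. Counting usable data out of all 30 is also a legitimate quantity for planning a later trial.

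All of this stands, but it does not remove the point. The decision rule works on the bands, not on the descriptive report, and the bands mix the two causes. The missing stop band is a gap in a set of thresholds that the article otherwise prints in full.

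**Conclusion.** The point holds in limited form. The follow-up limb of completeness is confounded with retention: dropout alone that leaves fewer than 24 at a follow-up assessment costs success on two of six criteria, and the bands do not separate dropout from incomplete scales among returners. The double effect is confined to the success and amend bands.

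How closely the two criteria move together depends on the unknown rate of incomplete forms. Under monotone dropout they agree fully if there are none, and in about 58% to 88% of simulated trials at the assumed 5% to 10%. The article does not say whether a partly blank survey counts as completed for retention. If it does not, the overlap is closer than these figures suggest.

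Two further defects need no assumption. Completeness below 75% at baseline or below 60% at follow-up is unclassified and cannot count towards stopping. The baseline amend count, as printed, overlaps success. These are inexpensive faults in a printed decision rule and should be corrected.

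**What to change.** 1. Print the baseline amend band as 23-26/30.
2. Add stop bands for completeness: below 75% at baseline (22/30 or fewer), and below 60% at follow-up (fewer than 18/30, or the matching percentage if the denominator changes).
3. Score follow-up completeness of the primary caregiver measures among participants who returned that assessment, and report the count out of all enrolled beside it. Success at 80% would then need 20 of 24, 21 of 26, 23 of 28 or 24 of 30. Case A above would be amend (78%) and Case B success (100%). With 24 returning and 22 complete, the result would be 22/24 = 92% instead of 22/30 = 73%.
4. If the denominator of 30 is kept, count retention and follow-up completeness as one criterion in the overall decision.

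The cost is the rewording of one criterion; the data are already being collected. The downside is that the completeness denominator then varies with retention, so it must always be reported. High completeness among few returners must not be read as good follow-up, which is why the count out of all enrolled belongs beside it. Since enrolment is under way, the change should be dated and made before follow-up results are tallied.
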